##### Specification of tailored exercise program

In the second component of the initial home visit, the exercise instructor (physiotherapists and sports scientists) first discusses with the participants why regular exercise is important (e.g. to attain own physical activity goals, to prevent further falls, to maintain autonomy). An individually tailored training schedule is compiled from a set of balance (standing, weight shifts, walking) and strength (chair rising) exercises with different intensities. For setting the exercise plan, tasks for each exercise component are performed from easy to difficult (based on the participants´ functional capacity and according to the exercise instructor’s assessment). The training protocol is outlined in Table 2. The exercise instructor chooses the tasks the participants are barely able to perform safely with supervision by the lay instructor. Other criteria being considered for final exercise selection are participants´ respective main and other impairments (cardio-pulmonary capacity, neurological symptoms, level of vision impairment and level of cognitive as well as mental capacity). The only provided equipment are low cost foam seat pads with different heights for the chair rising exercise, if necessary. The selected exercises are always repeated together with the lay instructor to ensure feasibility and safety. The exercises are defined and recorded using spreadsheets with tasks each ordered by difficulty.

**Table 2 Tab2:** Training protocol (adapted from [33])

Motor abilities/ skills and exercises	Static/ Dynamic balance (a) ‘Standing’ (b) ‘Weight shifting’ (c) ‘Walking’ Strength (d) ‘Chair-rising’	

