##### Visits of the lay instructors

After the initial home visit, regular home visits with exercise supervision by the lay instructor are conducted over four months with a frequency of two times per week. Each home visit takes maximally two hours including (a) 30 min for exercises, (b) practicing of at least one further physical activity according to the participant’s personal goals and (c) additional time for unstandardized interaction (e.g. conversation) comparable to usual visits provided by visitor services. All home visits and supervised exercises are recorded by the lay instructor. In accordance to previous work on peer-delivered physical activity and exercise interventions [41, 42], the authors could show in the pilot study with 17 cognitively impaired hip and pelvic fracture patients that the designed intervention approach with lay instructors is feasible and effective ([name], [name]: Hip fracture and cognitive impairment: Pilot study of a post-rehabilitation exercise program, unpublished).

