#### Interventionists

The exercise instructors in *Module 1* are physiotherapists and sports scientists, called exercise instructors, who are experienced in rehabilitation of cognitively impaired older adults. After an initial training, they are supervised by a clinical psychologist (KP) or a senior sports scientist (KH) both with long-standing experience in fall prevention, exercise programs and rehabilitation.

The interventionists in *Module 2* are a social worker and a gerontologist both highly experienced in counselling for older adults and family caregivers. Like the therapists in *Module 1* they received an initial training and are supervised by clinical psychologists (KP, MS) during the intervention period of the study.

The lay instructors have been recruited from different sources (visitor services for people with dementia, sports clubs, municipal elderly council, local newspapers, churches, public lectures on physical activity in older age). For their engagement, they get expense allowances according to the standards of local visitor services at the two recruitment sites. Before participating in the intervention, they are trained in two 4-h group sessions with a maximum of 12 participants. Every course is held together by an exercise instructor and a gerontologist. The components of the intervention delivered by the lay instructors are presented in lectures and exercises. Key elements are the exercise protocol, basic understanding about training control and progression, motivational aspects, use of walking aids, safety issues during exercising, medical or emotional exercise termination criteria and important aspects in the interaction with cognitively impaired persons.

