### Adverse events

In this trial a serious adverse event (SAE) is defined as any harmful disease or injury, fall-related or not, that leads to hospital admission or death [83]. Furthermore, all falls which happen during assessment or intervention independent of severity are recorded as SAE as well. Any minor or temporary clinical symptoms are only recorded as adverse events if they result in considerable restricted daily activities (e.g. staying in bed) for more than one week. All SAEs are documented according to the trial protocol. SAEs within the intervention and SAEs that requires further action beyond the study protocol (e.g. involving local services because the patient is not able to organize additional support) are directly discussed with the investigators (KP, KH, MS). In addition, the SAE documentation is discussed annually with at least one member of the independent data and safety monitoring committee (DSMC).

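### The one-week threshold keeps short-lived symptoms that stop an exercise session out of the adverse-event record, and injuries outside sessions that do not lead to admission have no stated category

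*Protocol article*

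**What the plan says.** The Adverse events section of the protocol article gives three recording routes.

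- An SAE is "any harmful disease or injury, fall-related or not, that leads to hospital admission or death".
- In addition, "all falls which happen during assessment or intervention independent of severity are recorded as SAE as well".
- For lesser complaints the section sets a threshold: "Any minor or temporary clinical symptoms are only recorded as adverse events if they result in considerable restricted daily activities". The restriction has to last longer than a week, and being confined to bed is the example given.

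The same section has the SAE documentation discussed once a year with at least one member of the data and safety monitoring committee (DSMC).

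Other sections bear on how these routes work:

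- **Specification of tailored exercise program:** "The exercise instructor chooses the tasks the participants are barely able to perform safely with supervision by the lay instructor".
- **Table 2 (Training protocol):** there are 35 supervised sessions, 32 with the lay instructor alone and 3 with the lay instructor and the interventionist together.
- **Interventionists:** lay instructors are trained in two 4-hour group sessions, which cover "medical or emotional exercise termination criteria" among other topics.
- **Visits of the lay instructors:** "All home visits and supervised exercises are recorded by the lay instructor". The section Adherence to intervention protocol uses such records to define non-adherence.
- **Falls:** falls are collected in both arms by calendar and weekly telephone calls. The section defines a fall but states no class of injury.

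**The concern.** The protocol tests whether exercise near the limit of a frail, cognitively impaired patient's ability can be led by trained lay people, and its Discussion looks ahead to use in visitor services. The same Discussion says that physical and mental overload of these patients must be avoided. A session stopped for symptoms is the most direct sign of overload that the trial can observe. The protocol has criteria for stopping and a record of each session, but nothing links a stopped session to safety reporting, and the one-week rule excludes most such episodes.

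The programme also promotes activity and unsupervised self-exercise. Harm from these arises outside supervised visits, where an injury counts as an SAE only if it leads to admission or death.

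The safety statement is at stake. Tolerability of the lay-led sessions could look better than it was, and a difference between arms in fractures managed without admission could be missed.

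**Working it through.** The protocol gives no event rate for any of this, so the check is mainly a reading of the rules case by case.

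1. **Fall during a supervised session or an assessment, with or without injury.** SAE whatever the severity. No gap.
2. **Injury or illness at any time that leads to admission or death.** SAE. No gap.
3. **Symptom that stops a session, no fall, settled within a week.** Not an SAE. Excluded as an adverse event by the one-week rule. The session is recorded, but no stated rule makes the stop or its reason a safety item. *Gap (a).*
4. **Fracture or other injury from a fall outside a session, not admitted.** Not an SAE. The fall is counted as an outcome. The injury becomes an adverse event only if it is read as a minor or temporary symptom and restricts activity for more than a week. *Gap (b).*
5. **Fall without injury outside any visit.** Counted as a fall in both arms, not an SAE.

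**Symmetry of SAE counts.** Cases 1 and 5 can be the same physical event. Assessment visits take place in both arms, so that part of the rule is balanced. Supervised sessions take place only in the intervention arm: 35 visits of at most 2 hours give up to 35 × 2 = 70 hours per participant in which a harmless fall is an SAE. The control arm has no such hours.

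**Exposure behind gap (a).**
- Share of sessions without a professional present: 32/35 = 91%.
- Full attendance by all 120 intervention participants: 120 × 35 = 4,200 sessions.
- Lower scenario: 85 participants per group (the number required before the drop-out allowance), each at the adherence minimum of 2 joint plus 19 lay visits: 85 × 21 = 1,785 sessions.

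**Illustration only, on assumed rates that are not in the documents.**
- If 0.5% to 2% of sessions are stopped for symptoms: 4,200 × 0.005 to 0.02 = 21 to 84 stops, or 1,785 × 0.005 to 0.02 = about 9 to 36.
- For gap (b), follow-up from T1 to T3 is 4 + 3 = 7 months. Person-years are 240 × 7/12 = 140, or 170 × 7/12 = about 99 with 85 per group.
- Assume 1 to 2 falls per person-year, 5% to 10% of them with a fracture, and one third of those not admitted. Then 140 × 1 × 0.05 × 1/3 = 2.3 to 140 × 2 × 0.10 × 1/3 = 9.3 fractures over both arms. With 99 person-years the range is about 2 to 7. These figures include falls during sessions, which are already SAEs, so they overstate gap (b) on these rates.

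**The case against.** The strongest reply starts from the second SAE rule. For balance training near the limit, a fall in the session is the main acute hazard. The protocol records every such fall as an SAE, even without injury, and SAEs within the intervention are discussed directly with the investigators. Falls elsewhere are collected weekly in both arms. Pain is measured, hospital days and rehabilitation services are recorded, and the exercise instructor telephones each intervention participant five times for feedback. Under Ethics and dissemination, the DSMC also reviews trial progress and efficacy endpoints, so it is not confined to SAE listings. A threshold for transient symptoms in frail patients after a fracture is an openly stated choice. The article refers to a fuller trial protocol that may classify injuries.

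Much of this stands. A reader might infer that harm counts only if it causes admission, death or more than a week of restriction; the rule on in-session falls contradicts that. A reader might infer that fractures managed without admission go unrecorded; the fall itself is recorded, and a fracture that restricts activity for more than a week could meet the adverse-event rule. A reader might infer that such fractures are graded as minor; the document has no severity grading and leaves them without a category. Nor can one say that the trial would show few exercise-related harms whatever the truth.

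The reply does not remove gap (a). The one-week rule is an explicit exclusion, so it is not a detail left to a longer document. None of the other data sources is stated to capture why a session was stopped.

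**Conclusion.** The point holds in limited form.

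- **Gap (a) is firm.** Following the stated rule, a symptom that stops a session without a fall and resolves within a week is not an adverse event.
- **Gap (b) is real on the text but softer.** The article gives no explicit category for an injury outside a session without admission, and the fuller protocol may supply one.
- **The asymmetry follows from the design.** The rule on falls during intervention can add SAEs in the intervention arm only, while gap (a) leaves out tolerability problems in that same arm. A comparison of total SAEs between arms is therefore hard to read.

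The size cannot be derived from the documents. The exposure is between about 1,785 and 4,200 supervised sessions in the two scenarios. The counts of stopped sessions and fractures rest wholly on assumed rates and carry no weight in the conclusion. The weakness lies in safety reporting and does not affect the primary analyses. It should be corrected or, if too late, disclosed.

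**What to change.** Amend the Adverse events section in two places. Both concern recording only.

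1. Record every new fracture and every fall injury that receives medical attention, whether or not the patient is admitted. Use one scripted question in the weekly falls calls that both arms already receive, and report the result by arm.
2. Mark each supervised session stopped under the termination criteria, with its reason, on the record that the lay instructor already keeps. Report these as an intervention-arm tolerability table per 1,000 sessions, separate from the between-arm comparison.

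When SAEs are reported, show falls during intervention visits on their own line, so that the remaining SAEs can be compared between arms on the same definition.

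If collection is still open, the cost is one question, one field and a short amendment. The downside is a longer list of events. Eligibility screening ended in February 2018; adding up to 6 weeks after discharge and 7 months of follow-up puts the last assessments at about the end of 2018, so collection was probably complete when the article appeared in April 2019. In that case, code both items from existing call and session records where those contain the information, say how complete that coding is, and state the one-week threshold as a limit on any safety conclusion. Coding existing records takes more work than a prospective question and may be incomplete.

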### Sample size

For sample size calculation, a two-step method was used. First, the sample size (N) was calculated as if a t-test on the T2 scores will be carried out, then the number of subjects was multiplied by a “design factor: (1 - ρ^2^)*N” (ρ = correlation between the outcome measured at baseline and at follow-up) to produce the number of subjects required for calculating an ANCOVA [84].

The estimated effect size calculation is based on the measured daily walking time (activPAL™) in a previous hip and pelvic-fracture study (ISRCTN79191813) as well as on the following assumptions: (a) daily mean walking time (completer, control condition with standard care) at discharge (M = 35.5 Min, SD = 27.9 Min); (b) daily walking time on average four months post-discharge from rehabilitation (M = 44.9 Min, SD = 34.8 Min); (c) a correlation of ρ = 0.45 between baseline and follow-up data; (d) an intended significant improvement of daily walking time of 30% (13.5 Min) which corresponds to an effect size Cohen’s d = 0.39; (e) β = .80 (power) and (f) α = .05 for two-sided testing.

The required number of cases for a two-sided t-test for independent samples is 106 persons in intervention and control group respectively (G*Power 3.1.9.2 [85]). The adjusted number of cases for the ANCOVA with the same power as for the t-test results in 85 persons per group [design factor: (1–0.45^2^)*106].

Using the data of the previous study in the same way for the SPPB, the design factor for this other primary outcome is lower (1–.64^2^). This means that with a sample size of 85 per group smaller effects for SPPB can be detected (Cohen’s d = 0.33) compared to the daily walking time (Cohen’s d = 0.39). Based on previous studies with hip or pelvic fracture patients a drop-out rate of 22.5% until T3 is expected. Therefore, the adjusted required number of cases is calculated with 110 patients in each group.

At the time of finalizing the study protocol for publication, an adjustment of the required sample size had been made (120 participants in each group) due to a higher drop-out rate than assumed before. Several participants had to be excluded because they went to short-term care after discharge from rehabilitation and could not return home later on.

### Data analyses

Descriptive analyses will be carried out to present baseline characteristics of both groups. Treatment effects on primary and secondary endpoints at T2 (after intervention) and T3 (at follow-up) will be analysed with analyses of covariance (ANCOVA), using baseline scores at t_1_ as covariates. In addition to intent-to-treat and completer analyses, subgroup analyses are planned (participants with pelvic fracture, MMSE total scores < 24, fear of falling, significant depressive symptoms). Since intent-to-treat analyses may underestimate active intervention components, the conduction of additional analyses (e.g. complier average causal effect) depending on type, randomness and degree of non-compliance is planned [86].

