## Background

The high incidence of fall related hip and pelvic fractures as well as the associated negative consequences have been widely described in the literature [1–4]. Mortality rates after hip-surgery are 5 to 10% within 30 days and about 33% after one year [5]. Within six months after fracture, only 40 to 70% regain their prior independence for basic activities of daily living (ADLs) [1]. Between 10 to 20% of hip fracture patients are dependent on long-term care and institutionalised as a consequence of the fracture [1]. Thus, high socioeconomic burden beyond acute care and rehabilitation is apparent [6]. Demographic changes in the future indicate further increases in health and social costs for this patient group [7].

Previous research has identified several predictors for reduced or delayed functional recovery after hip fractures. This includes high age, low pre-fracture level of functioning, reduced walking ability, high prevalence of comorbidities and certain fracture types (e.g. inter−/subtrochanteric versus cervical) [8, 9]. Other factors are fear of falling [10], depression [11, 12] and cognitive impairment [13, 14].

Over 40% of all patients with fall-related hip fracture are cognitively impaired [15]. These patients show poorer mobility outcomes and higher ADL dependence one year after the fracture [13, 16], and in consequence a significantly increased risk of nursing home admission [13].

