### Recruitment

All hip and pelvic fracture patients admitted to the geriatric rehabilitation departments of the Robert-Bosch-Hospital Stuttgart and the Agaplesion Bethanien Hospital Heidelberg (both Germany) were assessed for eligibility from July 2015 to February 2018. To include patients with complications after fracture or surgery, a maximum interval of 3 months between fracture event and admission to rehabilitation was allowed. Patients who had completed any orthopaedic rehabilitation during this time interval were not assessed.

After medical clearing, the screening and the recruiting were planned within the first two weeks of inpatient rehabilitation and done by trained physiotherapists and sports scientists. If it was unclear that the participant could return home the final screening and recruitment procedure was postponed to the third week. Close communication was maintained with the patient, caregiver as well as rehab staff, to avoid unexpected discharge management to nursing home.

Inclusion criteria were a hip or pelvic fracture within the last three months, mild to moderate cognitive impairment (Mini-Mental State Examination score of 17–26 [23]), age ≥ 65 years, minimum visual acuity (corrected vision, Snellen fraction > 20/400), living in home environment or assisted living and ability to walk 4 m with or without walking aid. Exclusion criteria were delirium (identified by the Confusion Assessment Method [24]), severe somatic or mental illness, terminal disease, moderate to severe aphasia (except amnestic aphasia) or severe apraxia, insufficient hearing ability for receiving calls or no telephone accessibility, insufficient knowledge of German language, and place of residence outside the Stuttgart and Heidelberg area, respectively.

Positive screened persons were informed in verbal and written form about the study program and asked to give written consent. The whole procedure was conducted in a comprehensible way according to the recommendations of Appelbaum [25]. Existing legal guardians or authorized representatives were involved in the information and consent process in any case, otherwise the closest family member if possible.

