### Outcome measures

Assessments were carried out at 4 measurement time points: -T1 (end of inpatient rehab, only participant), T1 (pre-intervention at participant’s home: week two to six post-discharge), T2 (post-intervention at participant’s home: 4 months after T1) and T3 (follow-up at participant’s home: 3 months after T2). The assessment at -T1 was performed to evaluate the further recovery process between rehabilitation and pre-intervention assessment (T1) and to identify predictors for short-term care and nursing home transition. Because of very short-term decisions on reimbursement of costs for extra rehabilitation time (usually one week or some days of ambulant rehabilitation) added to the 3-week standard rehabilitation regimen it was not possible to deliver the assessment in all cases within a narrow timeframe before discharge. Otherwise these patients have had to be excluded or assessed twice within a week.

Table 3 (participant) and Table 4 (participating caregiver) are outlined according to the SPIRIT Statement [47] and provide an overview of the assessments being performed at the defined measurement time points.

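### The stated ANCOVA names only T1 scores as covariates; adding a few pre-specified prognostic variables already on file would be a cheap, modest gain in precision for walking time

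*Protocol article*

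**What the plan says.** - **Data analyses.** Treatment effects on primary and secondary endpoints at T2 and T3 are to be estimated by "analyses of covariance (ANCOVA), using baseline scores" taken at T1. No other covariate is named. Pelvic fracture, MMSE below 24, fear of falling and depressive symptoms appear in the same paragraph, but as subgroups.
- **Sample size.** The trial is sized on that same single-covariate model. It takes "a correlation of ρ = 0.45 between baseline and follow-up data" for walking time and 0.64 for SPPB, and multiplies the t-test sample size by one minus the squared correlation.
- **Background.** "Previous research has identified several predictors for reduced or delayed functional recovery after hip fractures". The list includes high age, reduced walking ability, fear of falling, depression and cognitive impairment. No strengths are given, and time since fracture is not on the list.
- **Recruitment.** Age and MMSE are inclusion criteria, so both are known for every participant. For the fracture date, "a maximum interval of 3 months between fracture event and admission to rehabilitation was allowed".
- **Outcome measures.** The baseline visit is "T1 (pre-intervention at participant’s home: week two to six post-discharge"). SPPB is a primary outcome, so using T1 scores as covariates implies that a T1 SPPB exists.

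**The concern.** At a correlation of 0.45 the T1 walking time explains about 20% of the follow-up variance, and about 80% stays in the error term. For SPPB the corresponding share explained is 0.64² = 41%. Walking time is therefore the outcome with more to gain from further adjustment.

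Patients also reach T1 at different distances from the fracture. The article allows 0 to 3 months (about 13 weeks) to admission, then a standard 3 weeks of rehabilitation, sometimes up to a week more, then 2 to 6 weeks at home. The permitted range is about 0 + 3 + 2 = 5 weeks to 13 + 4 + 6 = 23 weeks. Two patients with equal T1 walking time at the two ends of this range may differ in how much they will still improve. The documents do not show this or give the actual spread, so it is a reason to include the variable and not evidence of its strength.

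At stake is precision. Recruitment has ended, and drop-out was higher than assumed. Variables already recorded could narrow the confidence interval and remove chance imbalance between the arms without new patients, but only if they are fixed in advance.

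**Working it through.** **Inputs (Sample size section)**
- Planning baseline, walking time: "at discharge (M = 35.5 Min, SD = 27.9 Min").
- Planning follow-up: "on average four months post-discharge from rehabilitation (M = 44.9 Min, SD = 34.8 Min").
- Effect: 30% of 44.9 = 13.47 min, stated as 13.5.
- Correlation 0.45; two-sided 5%; 80% power; drop-out 22.5%.

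**1. The plan's own figures reproduce**
- d = 13.5/34.8 = 0.388; the two-sided t-test needs 105.3, so 106 per group.
- 106 × (1 − 0.45²) = 106 × 0.7975 = 84.5, so 85 per group.
- 85/(1 − 0.225) = 109.7, so 110 per group, later raised to 120.

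**2. Power without charging for covariates**

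Non-centrality = d√(n/2)/√(1 − R²), with d = 13.47/34.8 = 0.387 and n = 85, so d√(n/2) = 2.523. At R² = 0.2025 the non-centrality is 2.523/√0.7975 = 2.826 and power is 80.2%. At total R² of 0.25, 0.30 and 0.35 power is 82.6%, 85.1% and 87.5%. These three figures are optimistic because they treat the extra coefficients as costless.

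**3. Power after charging for them**

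With k covariates and N = 170, chance covariate imbalance inflates the variance by 1 + k/(N − k − 3), and the residual degrees of freedom are N − 2 − k.
- T1 score only (k = 1): factor 1 + 1/166 = 1.0060, 167 df.
- T1 score plus four (k = 5): factor 1 + 5/162 = 1.0309, 163 df.
- Relative cost: 1.0309/1.0060 = 1.0247, about 2.5% of variance.

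| Model for walking time | Added R² (assumed) | Non-centrality | Power |
|---|---|---|---|
| T1 score only | – | 2.817 | 80.0% |
| plus four covariates | 0 | 2.783 | 79.0% |
| plus four covariates | 0.05 | 2.875 | 81.5% |
| plus four covariates | 0.10 | 2.976 | 84.1% |
| plus four covariates | 0.15 | 3.089 | 86.7% |

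Break-even added R² = 0.7975 × (1 − 1/1.0247) = 0.019, about 0.02.

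**4. Sensitivity to the correlation**

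The 0.45 links discharge to about four months after discharge in a previous study. The trial's own pair is T1, at home 2 to 6 weeks after discharge, and T2, four months later. The T1–T2 correlation is therefore not known. At an assumed 0.60, R² = 0.36, the T1-only non-centrality is 2.523/√(0.64 × 1.0060) = 3.145, and power is already 87.8%. An added R² of 0.10 in the planning case is 0.10/0.7975 = 12.5% of the residual variance. The same share of a residual of 0.64 is 0.080, which gives 2.523/√(0.56 × 1.0309) = 3.32 and power of 91.0%. The gain is then 3.2 points, against 84.1 − 80.0 = 4.1 points in the planning case.

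**The case against.** The strongest case against is that nothing here is wrong. Baseline-adjusted ANCOVA is valid, the trial is sized on that model, and the figures reproduce. A journal article condenses its plan: one sentence covers every endpoint and does not say that T1 scores are the only covariates. A separate analysis plan may add others. This stands as a limit on weight. It does not remove the point, because the article does state a covariate set and sizes the trial on it, and a better choice is available from recorded data.

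Several stronger readings are tempting, and the documents do not support them:
- **That strong predictors are being ignored.** The Background gives no strengths and speaks of functional recovery after hip fracture, not of sensor-measured walking time given its T1 value. MMSE is restricted to 17–26 by the entry criteria, and T1 walking time already carries much of walking ability.
- **That the gain is free.** Estimating four more coefficients costs about 2.5% of variance, so covariates that explain nothing lower power.
- **That 20% is this trial's figure.** It comes from a different pair of time points in another study.
- **That covariates are the only remedy for drop-out.** Enrolment was raised to 120 per group, which leaves 85 analysable at up to 1 − 85/120 = 29% loss.
- **That each outcome should simply be adjusted for the other.** Putting T1 walking time into the SPPB model would make that analysis depend on a usable three-day recording from each patient. This could lose patients from the outcome that is already better explained.

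**Conclusion.** The point holds as a low-cost efficiency recommendation of modest priority. The analysis as stated is valid.

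Under the planning values (85 per arm, d = 0.387, correlation 0.45), four pre-specified covariates change walking-time power by about −1.0 point if they add nothing, and by +1.5, +4.1 or +6.7 points at an added R² of 0.05, 0.10 or 0.15. The change pays for itself above an added R² of about 0.02. All added R² values are assumptions. The gain is likely to be smaller if the true T1–T2 correlation exceeds 0.45, because less variance is then left to explain. If a separate analysis plan already fixes such covariates, the point is met.

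**What to change.** Before unblinding, add a statement to this effect to the analysis plan:
- Both primary models adjust for the outcome's own T1 score, age, MMSE at screening and time from fracture to T1. The walking-time model also adjusts for T1 SPPB.
- T1 walking time is not required in the SPPB model. If it is wanted there, missing baseline covariate values are filled by simple imputation so that no patient leaves the analysis. The same imputation rule covers any other missing added covariate.
- The model with only the T1 score is kept as a sensitivity analysis.

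Randomisation took place before discharge, so the T1 date, like the T1 score that the plan already uses, falls after allocation but before the intervention. If the timing of T1 could have differed between arms, time from fracture to randomisation is the safer version of that covariate.

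The cost is a short addition to the plan and no new data, with about 1 percentage point of power at risk if the covariates prove uninformative. If unblinding has already happened, the extended model should be reported only as a supporting analysis, because the covariates could then be chosen with the result in view.
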